### Patient and public involvement

3.14

Patients and/or public were not involved in the design of this study.

## Discussion

4

Stroke is the principal incapacitating disease in adults,^[1]^ and the importance of optimizing strategies to rehabilitate patients affected by this disease is evident. Mobility improvement is the primary objective for most patients and therapists since it is essential for the independence of these individuals.^[31]^

Several studies have shown that AFO use produced improvement in the cadence and velocity of the gait by minimizing knee hyperextension along with improvements in symmetry and stability in these patients.^[32]^ Although there are some studies that report efficacy of AFO in these hemiplegic patients, research on its effects in relation to mobility, and to balance is scarce^[33]^; furthermore, there is no consensus on which AFO model is more efficacious for treating this pathology.

The results of this study will contribute to clinical practice by identifying the type of AFO orthosis that is more suitable for this condition, helping to standardize prescription of these orthoses by professionals, and guiding future research studies on this subject, which is still incompletely defined in the literature.

Our goal is to accomplish a randomized clinical trial of high quality that utilizes validated evaluation measures not only for balance and mobility in our primary outcomes but also for the levels of anxiety and depression in our secondary outcomes. If 1 of the AFO types is proven to be superior to the other in some of these aspects, this evidence would permit professionals to recommend the ideal AFO for patients with stroke sequelae, which will minimize their incapacity and optimize their rehabilitation. For our results to generate an impact on the clinical practice of therapists and on patient care, they should be publicized at congresses and in academic journals pertaining to this research area.

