### Randomization and blinding

3.5

The process of randomization will be performed using Microsoft Excel for Windows by a researcher who was not involved in the recruitment of participants. The participants will be randomized into 2 groups at a proportion of 1:1 with 25 patients allocated into each group. After evaluation, the participants who are eligible for the study will be referred to a physiotherapist responsible for their specific evaluation.

Because of the nature of the interventions, it will be impossible to blind the therapists and patients involved in the study.

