### Secondary outcome measures

3.8

The secondary outcomes will be the quality of life and the levels of anxiety and depression after the intervention, which will be evaluated by the Euroqol and HADS, consecutively. Additional secondary outcomes include the incapacity level, the degree of neurological deficit severity, the functional capacity for basic daily life activities and spasticity of the lower limb affected after the stroke, which were evaluated using the mRs, NIHSS, BI, and mAS.

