### Sample size calculation

3.9

The sample will be composed of 50 volunteers randomized into 2 groups to receive 1 of 2 types of AFO. This number of participants are capable to detecting a 30% difference in improvement of the primary outcome (TUG and TSMB) with an alpha error of 0.05 and beta error of 0.2.

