### Statistical analysis

3.13

The analyses will follow the principle of Intention to Treat. The Kolmogorov-Smirnov test will be employed to verify the normality of the distribution. The non-categorical data of a parametric distribution will be analyzed by two-way ANOVA for repeated measures, and multiple comparisons will be analyzed with the Tukey test. The categorical data at the baseline moment will be compared using the Chi-Squared test. The nonparametric distribution variables will be categorized as improvement or worsening and compared between groups with the Chi-Squared test. The non-categorical data will be expressed as means and standard deviations, and the categorical data will be expressed as percentages. Statistical significance will be established as *P* < .05.

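### The Discussion lets a difference in anxiety or depression alone support recommending an AFO type, even if TUG and TSMB show none

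*Protocol article*

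**What the plan says.** Section 3.7 of the protocol article makes balance and mobility primary, measured by TUG and TSMB. Section 3.8 makes quality of life (Euroqol) and anxiety and depression (HADS) secondary, and then adds four more instruments (mRs, NIHSS, BI, mAS): "Additional secondary outcomes include the incapacity level, the degree of neurological deficit severity, the functional capacity for basic daily life activities and spasticity" of the affected leg. That makes six secondary instruments.

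Section 3.13 gives one threshold for the whole analysis: "Statistical significance will be established as *P* < .05". The only multiple-comparison method named there is Tukey's test, which belongs to the repeated-measures ANOVA and does not act across outcomes.

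The Discussion (section 4) says that the trial uses validated measures for balance and mobility as primary outcomes, "but also for the levels of anxiety and depression in our secondary outcomes". The next sentence supposes that one AFO type is shown superior in some of the aspects just listed, and concludes that "this evidence would permit professionals to recommend the ideal AFO for patients with stroke sequelae".

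**The concern.** The aspects that the recommendation sentence refers back to are the four in the sentence before it: balance, mobility, anxiety and depression. Two are primary and two are secondary. The condition is met by superiority in some of them, and nothing says that a primary must be among them. With a single P < .05 for every outcome, a secondary result then has the same standing as a primary one when a device is recommended.

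At stake is what the trial may conclude. If TUG and TSMB show no difference and one HADS subscale falls below .05, the text would allow one AFO type to be presented as the better one. The sample size in section 3.9 is justified on TUG and TSMB only, so that conclusion would rest on an outcome for which the trial was not sized, and the false-positive chance of this route can exceed the 0.05 stated for each test.

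**Working it through.** **Inputs from the protocol article**
- Threshold per test: 0.05 (section 3.13).
- Primaries: 2, TUG and TSMB (section 3.7).
- Secondary instruments: 6 (section 3.8).
- HADS: 7 depression and 7 anxiety questions (section 3.11), so 1 or 2 tests depending on how it is scored. The article does not say which.

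**Assumptions**
- No true difference on any outcome, and two-sided tests.
- The correlation between test statistics is not given. The values used are 0 (independent), 0.5 and 0.8, the same for every pair.

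**The plan's own figure.** The article states no false-positive rate for this route, so there is none to reproduce. Its sample size of 50 cannot be reproduced either, because no standard deviation or base rate is given. This point does not depend on it.

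**Formulas.** Let N(k) be the probability that none of k tests reaches P < .05.
- Independent tests: N(k) = 0.95^k.
- Common correlation r: N(k) is the average over a standard normal u of [Φ((1.96 − √r·u)/√(1−r)) − Φ((−1.96 − √r·u)/√(1−r))]^k, by numerical integration.
- At least one false positive among k tests: 1 − N(k).
- Both primaries non-significant and at least one of k secondaries significant: N(2) − N(2 + k).

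**Step 1: the route the Discussion names (anxiety or depression)**

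Independent: 1 − 0.95² = 1 − 0.9025 = 9.75%. With both primaries also non-significant: 0.95² × (1 − 0.95²) = 0.9025 × 0.0975 = 8.8%.

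| | r = 0 | r = 0.5 | r = 0.8 |
|---|---|---|---|
| At least one HADS subscale false positive | 9.75% | 9.1% | 7.8% |
| The same, with both primaries non-significant | 8.8% | 6.5% | 3.6% |

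If HADS is analysed as one score, the first row becomes 5% whatever the correlation. The second row becomes 0.9025 × 0.05 = 4.5% if independent, and less if correlated.

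**Step 2: the wider route, only if any of the six secondary instruments could drive the recommendation**

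Independent: 1 − 0.95⁶ = 1 − 0.7351 = 26.5%. With both primaries also non-significant: 0.9025 × 0.2649 = 23.9%.

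| | r = 0 | r = 0.5 | r = 0.8 |
|---|---|---|---|
| At least one of six false positive | 26.5% | 20.7% | 13.9% |
| The same, with both primaries non-significant | 23.9% | 15.9% | 7.9% |

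The recommendation passage names only anxiety and depression among the secondaries, so Step 1 is the relevant size.

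**The case against.** The strongest reply has three parts.

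First, rules for secondary multiplicity are commonly left to a statistical analysis plan. That plan is not shown, and a journal article condenses the full protocol. This stands: the lack of an adjustment, a testing order or an exploratory label is not a finding by itself. It does not dispose of the point, because the Discussion makes a positive statement about what would support a recommendation, and an adjustment set out elsewhere would not alter that statement.

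Second, the sentence describes the hoped-for impact of the trial. It sets no success criterion, cites no P value and does not say that one HADS result with null primaries is enough. This also stands, and it limits the claim: the text permits a secondary result to support a recommendation, but it does not lay down that such a result decides one.

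Third, the article does rank its outcomes. It labels anxiety and depression as secondary in the very clause at issue, and its sample size statement refers to TUG and TSMB. That is correct, but the ranking is not carried into the sentence on the recommendation, which treats the listed aspects alike.

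A reader might also infer that a spurious secondary finding is likely, or that the risk is 20% or more. The documents do not support that. Figures of that size need all six instruments to be able to drive the recommendation, and Euroqol, mRs, NIHSS, BI and mAS are not named there. Even the largest six-instrument figure, 26.5%, is well short of likely.

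**Conclusion.** The point holds in limited form. As written, the Discussion allows a difference in anxiety or depression to support recommending one AFO type when TUG and TSMB show no difference, and section 3.13 tests that difference at the same .05 as the primaries.

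On that route the chance of a false positive is 7.8% to 9.75% with two HADS subscales, or 5% with a single score. Occurring together with two non-significant primaries, the two-subscale figure is 3.6% to 8.8%. These figures assume no true differences, two-sided tests and a common correlation between 0 and 0.8. The correlations and the scoring of HADS are assumptions, not facts from the article.

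The excess over 5% is modest, and it vanishes if HADS is one score. The main defect is therefore the standing given to a secondary outcome rather than the inflation. It should be corrected, but it does not affect the design, the data collected or the sample size.

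**What to change.** - **Discussion:** make any recommendation of an AFO type depend on the primary outcomes, TUG and TSMB. Anxiety and depression may be mentioned as adding to the picture, not as sufficient grounds.
- **Sections 3.8 and 3.13:** state that all secondary outcomes are supportive and are reported as between-arm differences with 95% confidence intervals.
- **If a confirmatory claim on anxiety or depression is wanted:** test the two HADS subscales in a stated order, and only after a positive primary result. This closes the route when both primaries are non-significant.

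The cost is wording in three places, with no new data, visits or patients. The downside is that an isolated secondary P < .05 can be reported only as hypothesis-generating.

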## Trial status

5

At the time of submission, recruitment was ongoing. Recruitment started on March 15, 2018 and is expected to be completed on November 30, 2019. It was registered by Brazilian Registry of Clinical Trials ReBEC (TRIAL: RBR-6SF2VV) on March 08, 2018 and is being financed by National Council for Scientific and Technological Development (CNPq) through process number 423924/2016-8.

(Appendices:).
